**3.2 Number of Participants**

We aim to recruit twenty women.

**3.3 Number of Centres**

St John of God Subiaco Hospital will be the only participating centre.

**3.4 Duration of study**

We plan to commence this study in January 2018, following ethical and governance approval. The anticipated time period for patient recruitment phase and data collection is 24 months. Data analysis would take an extra 6 months. The study will aim to be completed by July 2020.

**4 PARTICIPANT SELECTION**

**Patients receiving Optifast as part of standard of care must meet the following criteria.**

**4.1 Inclusion Criteria**

- Recommended by treating Gynaecological Oncologist to have VLCD prior to surgery
- Age ≥ 18 and ≤65 (outside these ranges, metabolic and physiologic adaptations to intensive diets are decreased)
- BMI ≥ 35
- Histologically confirmed grade 1 endometrioid adenocarcinoma on uterine curetting or endometrial biopsy (pipelle)
- No extra-uterine disease on pre-operative imaging of chest, abdomen or pelvis (any imaging modality allowed - X-ray, CT, MRI, PET)
- Patient wishes to lose weight
- Suitable for laparoscopic hysterectomy at surgeon’s discretion
- Ability to understand study requirements and attend regular appointments with dietitian or GP locally to monitor ketonuria, blood pressure and body measurements

**4.2 Exclusion Criteria**

- Any medical contraindication to use of VLCD, including lactation, presence of porphyria, severe hepatic disease, advanced renal disease, unstable cardiac disease (recent myocardial infarction or unstable angina), type 1 diabetes mellitus, overt psychosis, alcoholism or drug abuse^28^
- High alcohol intake based on NHMRC Australian Alcohol Guidelines^29^
- Patients in lithium, corticosteroids, anticonvulsants (although not a contraindication to Optifast, requires extra monitoring beyond the scope of this study)
- Evidence of extra-uterine disease clinically or on medically imaging
- Histological cell types including serous, clear cell, carcinosarcoma, sarcoma, de-differentiated
- Moderately differentiated or poorly differentiated (grades 2 and 3) endometrioid adenocarcinoma
- Inability to give informed consent
- Non English speaking
- European Cooperative Oncology Group (ECOG) performance status >3

**5 STUDY OUTLINE**

**5.1 Study flow chart**

Identification of motivated women with BMI ≥35 with a diagnosis of low risk endometrial cancer planned to undergo laparoscopic hysterectomy and meet inclusion/exclusion criteria requirements

🡻

Provision of written and verbal information regarding following a VLCD pre-operatively (including the Optifast Clinical Treatment Protocol booklet to discuss with their primary care giver/GP)

🡻

If interested, woman given patient information sheet and offered to participate in study

🡻

If woman agrees to study participation

Consent completed by treating gynaecologic oncologist

🡻

Enrolment into study and planned surgery date for 4-6 weeks

🡻

Nutritional assessment by dietician, Baseline fasting blood tests, anthropometric and blood pressure measurements

🡻

After 2 weeks of VLCD - contact with the dietitian/local GP to facilitate dietary adherence and success. Urinary ketones to assess dietary compliance. VLCD patient questionnaire.

Repeat anthropometric and BP measurements.

🡻

After 4 weeks of VLCD (if on 6 week program)– contact with dietitian/local GP, urinary ketones, VLCD patient questionnaire, anthropometric and BP measurements

🡻

On day of surgery (both 4 and 6 week patients)– repeat fasting blood tests, urinary ketones, VLCD patient questionnaire, anthropometric and BP measurements

🡻

Uterus, tubes, ovaries and any additional specimens sent to Australian Clinical Labs pathology for routine analysis

🡻

Data collection

🡻

Patient returns to normal diet and offered follow up with dietitian 1 month post operatively

**5.2 Scheduled Visits**

| Interventions | Enrolment Visit at initial consultation | Start VLCD | 2 weeks of VLCD | 4 weeks VLCD (if on 6 week program only) | On day of Surgery (both 4 and 6 week patients) |
| --- | --- | --- | --- | --- | --- |
| Informed Consent | ✓ |  |  |  |  |
| Inclusion/exclusion criteria, recording of history, physical exam | ✓ |  |  |  |  |
| Dietitian/ Anthropometric measures, BP |  | ✓ | ✓ | ✓ | ✓ |
| Fasting blood tests |  | ✓ |  |  | ✓ |
| Urine ketones |  |  | ✓ | ✓ | ✓ |
| Patient questionnaire re: VLCD |  |  | ✓ | ✓ | ✓ |
| Tissue collected for analysis |  |  |  |  | ✓ |

Not all of the above interventions are part of routine care for a patient diagnosed with an endometrial cancer. Whilst height, weight, BMI and BP are routine measurements at the initial consultation, anthropometric measures such as waist and hip circumference are not. All anthropometric measurements will be performed at baseline and fortnightly (on 2-3 occasions). Having a blood test (FBC, EUC, LFTs, CMP, coagulation profile, CA125) at baseline and on the day of surgery is routine (G&H) hence the additional tests particular to this research (uric acid, iron studies, fasting lipid profile -Total cholesterol, LDL, HDL, TG - fasting glucose metabolism -plasma glucose, plasma insulin, HBA1C -and 25OHVitD) required for the study can be performed at the time as the routine tests to avoid further invasive procedures. The patient will be required to provide a urine sample for urine ketone testing on 2-3 occasions. They will also be required to complete a 6 point likert questionnaire on 2-3 occasions. There will be fortnightly contact with the dietitian or local GP, either face-to-face or over the phone to facilitate dietary adherence and success.

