**2.2 Secondary Outcomes**

Secondary outcomes will include:

-Monitoring changes over the 4-6 week VLCD period in body weight, BMI, anthropometric measures (hip and waist circumference), blood pressure and serum biochemistry.

-Evaluating patient tolerability of the VLCD using a validated qualitative questionnaire.

-Collecting data on surgical outcomes.

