A validated questionnaire of product side effects and acceptability^22^ will be used. Subjects will be asked to rate 6 factors of product taste, hunger, nausea/vomiting, bowel function, emotional eating and social eating on a 5 point Likert scale (see appendices 10.2).

Anthropometric measurements of height (using a wall-mounted stadiometre), weight (wearing light clothing, no shoes), BMI (weight kg/height m^2^), waist circumference (narrowest point between low rib margin and iliac crest) and hip circumference (widest point over greater trochanters) will be recorded at baseline and fortnightly preferably by the same clinician or their appropriate delegate. Seated blood pressure will be measured at baseline and fortnightly. Blood tests will be taken at baseline and again on the day of surgery (after 4-6 weeks of Optifast) including FBC, EUC, LFTs, CMP, uric acid, CA125, iron studies, fasting lipid profile (Total cholesterol, LDL, HDL, TG), fasting glucose metabolism (plasma glucose, plasma insulin, HBA1C) and 25OHVitD.

All patients will be given instructions on pre operative fasting and be allowed clear fluids up to 2 hours and solids up until 6 hours prior to induction of anaesthetic as per ERAS recommendations. Randomized controlled trials on mechanical bowel preparation have shown no improvement in surgical exposure or bowel handling in laparoscopic gynaecologic procedures^34-35^.

For the laparoscopic hysterectomy, all patients will receive 2g Cephazolin and 500mg metronidazole 15-60 minutes prior to skin incision (as per eTG 2006). Clindamycin (or Lincomycin) 600mg can be used for patients who are allergic to penicillin.

Additional information will be recorded post operatively on:

- Tumour stage, grade, histological type, degree of myoinvasion
- Lymphadenectomy performed – Yes or No
  - Pelvic vs. para-aortic nodes
  - Sentinel lymph node biopsy vs. debulking of enlarged nodes vs. full pelvic lymph node dissection
  - Number of nodes removed
  - Number of nodes positive
- Adjuvant treatment recommendation from multidisciplinary meeting/tumour board
- ASA and Anaesthetic time
- Operating time
- Surgical complications – urinary tract, vascular or bowel injury; cardiac/pulmonary complications; wound breakdown; infection; estimated blood loss
- Length of hospital stay

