**Peripheral Nodes:**

**PELVIC EXAMINATION:**

**External Genitalia:**

**Vagina:**

**Cervix:**

**Uterus:**

**Adnexae:**

**Rectal:**

**COLPOSCOPY:**

**PROVISIONAL DIAGNOSIS:**

**INVESTIGATIONS:**

**TREATMENT:**

**10.2 Patient VLCD Questionnaire**

**Circle how many weeks of Optifast have you completed?**

| 2 | 4 | 6 |
| --- | --- | --- |

1. **How do you rate the product taste?**

| Highly unacceptable | Unacceptable | Tolerable | Acceptable | Highly acceptable |
| --- | --- | --- | --- | --- |
| 1 | 2 | 3 | 4 | 5 |

1. **How hungry are you?**

| Extreme Hunger | Hungry most days | Hungry some of the time | Occasional Hunger | No Hunger |
| --- | --- | --- | --- | --- |
| 1 | 2 | 3 | 4 | 5 |

1. **How much nausea or vomiting do you have?**

| Daily | 4-6 times/week | 2-3 times/week | ≤1 time/week | None |
| --- | --- | --- | --- | --- |
| 1 | 2 | 3 | 4 | 5 |

1. **How well are your bowels working compared to what is normal for you?**

| no bowel motion in the past 4 days | no bowel movement in the past 2-3 days | normal | increased frequency | diarrhoea |
| --- | --- | --- | --- | --- |
| 1 | 2 | 3 | 4 | 5 |

1. **How often are you emotional eating?** - Emotional eating defined as ‘eating foods outside the diet’s guidelines, due to emotional reasons such as stress, sadness, frustration, anger.

| Daily | 4-6 times/ week | 2-3 times/week | ≤ 1 time/week | None |
| --- | --- | --- | --- | --- |
| 1 | 2 | 3 | 4 | 5 |

1. **How often are you social eating?** - Social eating defined as eating foods outside the diet’s guidelines because you are in a social setting.

| Daily | 4-6 times/ week | 2-3 times/week | ≤ 1 time/week | None |
| --- | --- | --- | --- | --- |
| 1 | 2 | 3 | 4 | 5 |

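### The tolerability questionnaire is first given at 2 weeks, so hunger and nausea present before the diet, and partly bowel symptoms, cannot be told apart from effects of the VLCD

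*Protocol*

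**What the plan says.** Section 2.2 of the protocol lists "Evaluating patient tolerability of the VLCD" as a secondary outcome. Section 3.1 describes the instrument as "A validated questionnaire of product side effects and acceptability", with six factors rated on a five-point scale.

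Four places fix when it is given, and they agree:

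- **Visit table, section 5.2.** The row "Patient questionnaire re: VLCD" has ticks at 2 weeks, at 4 weeks for the 6-week programme, and on the day of surgery. The Enrolment and Start VLCD cells are empty.
- **Text of section 5.2.** "They will also be required to complete a 6 point likert questionnaire on 2-3 occasions".
- **Flow chart, section 5.1.** The step before the diet reads "Nutritional assessment by dietician, Baseline fasting blood tests, anthropometric and blood pressure measurements". It contains no questionnaire.
- **Form, section 10.2.** It opens with "Circle how many weeks of Optifast have you completed" and offers only 2, 4 and 6.

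Section 7.1 says the analysis will be descriptive. It gives no rule for attributing a reported symptom to the diet, and the protocol defines no side-effect rate.

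**The concern.** A side effect is something that appears or worsens after exposure. To show one, a study needs a comparison group or a score from before exposure. This study has no comparison group, and for the symptom items it has no earlier score. It does take weight, waist, hip, blood pressure and fasting bloods at the start of the diet.

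The ambiguity runs in both directions. Nausea that was already there may be read as intolerance of the product. A fall in hunger, which the background in section 1.1 suggests ketosis can bring, would not be visible.

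At stake is what the tolerability results can say. Section 1.2 makes documenting tolerability part of the reason for the study, and section 7.1 intends the findings to support the planning of a later randomised trial. The gap is in data collection. Once a woman has started the diet, her pre-diet score cannot be recovered by any later analysis plan.

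**Working it through.** **1. Does the schedule leave room for a baseline score?** Counting the ticks in section 5.2:

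- 4-week programme: week 2 + day of surgery = 2 occasions.
- 6-week programme: week 2 + week 4 + day of surgery = 3 occasions.

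This reproduces the stated 2-3 occasions exactly, so no unlisted baseline completion is implied. With a completion at Start VLCD the counts would be 2 + 1 = 3 and 3 + 1 = 4.

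**2. Which of the six items in section 10.2 have a meaning before the diet?**

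| Item | What it asks | Reference to the pre-diet state | Affected? |
| --- | --- | --- | --- |
| Taste | Rating of the product | None possible before use | No |
| Hunger | Current state | None | Yes |
| Nausea/vomiting | Current frequency | None | Yes |
| Bowels | Function against the woman's own normal | In the stem, but not in every answer | Partly |
| Emotional eating | Departures from the diet | None possible before the diet | No |
| Social eating | Departures from the diet | None possible before the diet | No |

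The nausea item, "How much nausea or vomiting do you have", is typical of the two clear cases: it records frequency now and nothing about before.

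The bowel item is mixed. Its stem and its middle answer refer to what is usual for the woman. Its lowest answer, "no bowel motion in the past 4 days", is an absolute state. A woman with long-standing constipation could truthfully choose the middle answer (3) by following the stem, or 1 or 2 by following the literal wording of the answers. The form does not settle which.

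**3. What does the missing score hide?** As an illustration on the form's own scale (5 is best), suppose three women each score 3 for nausea/vomiting at week 2. If their scores before the diet had been 5, 3 and 2, their changes would be 3 - 5 = -2, 3 - 3 = 0 and 3 - 2 = +1: worse, unchanged and better. Under the present schedule the three records are identical.

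**4. Can the week 2 score stand in for a baseline?** No. Section 3.1 says that urinary ketoacids rise after the first week of the diet, so by week 2 any effect of ketosis on hunger may already be present. Later scores show the trend within the diet, not the step from before it.

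**5. Does other pre-diet information fill the gap?** The initial visit form in section 10.1 has a free-text bowels heading and a yes/no screen for poor eating or poor appetite. The first gives some history but no score. The second concerns too little appetite, so it is not a baseline for a hunger scale. The form has no specific nausea item.

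**6. Size.** The documents give no prevalence of these symptoms before the diet and define no side-effect rate, so no bias can be calculated.

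**The case against.** The best case for the present plan is that tolerability is not defined as a change. Section 2.2 separates the variables to be monitored for change (weight, BMI, anthropometry, blood pressure, biochemistry) from the evaluation of tolerability, and baselines are scheduled for the former. How hungry or nauseated women feel while on the diet is a legitimate feasibility description in itself. Repeated scores also show the course within the diet, and section 1.1 cites an on-diet comparison of this kind, between weeks 4 and 10, from the source also cited for the questionnaire. The schedule is consistent across table, text, flow chart and form.

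Most of this stands. The on-diet scores are useful and should be kept, and the protocol does not contradict itself. What it does not answer is the label. Section 3.1 says the instrument measures side effects of the product, and an on-diet level alone cannot show that.

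A reader might go further and infer three things that the documents do not support:

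- *Pre-existing symptoms will be counted as effects of the diet.* No attribution rule is stated and the analysis is descriptive. The supportable statement is that the two cannot be distinguished.
- *A constipated woman must score 1 or 2 whatever the diet does.* The stem refers to her own normal and the form offers a normal answer. Bowel history is also taken at the initial visit. The bowel item is the weaker part of the point.
- *The side-effect rate is inflated by a set amount.* With 20 women each one is 1/20 = 5 percentage points, so assuming 2 to 4 women with prior symptoms would give 10 to 20 points. That number of women is an assumption without support in the documents. The rate is not an endpoint of the protocol, and the sum also requires every such symptom to persist and be reported as a side effect.

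**Conclusion.** The point holds in a limited form. The questionnaire is first given at 2 weeks in a single-group study, so prior hunger and nausea/vomiting, and to a lesser extent prior bowel symptoms, cannot be separated from effects of the VLCD. Taste, emotional eating and social eating are not affected.

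The direction of any bias is open and its size cannot be derived from the documents. The conclusion rests on two things: the 5.2 table is complete as printed, which the other three places support, and the study means to speak about side effects, as section 3.1 says. If the tolerability results were reported only as the level of symptoms during the diet, with no statement about cause, the loss would be smaller.

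The outcome is secondary and descriptive. The ketone-based primary outcome and the sample size are untouched. This is a cheap improvement to make before enrolment, not a flaw that undermines the study.

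**What to change.** Give the hunger, nausea/vomiting and bowel items at the existing Start VLCD visit, before the first product is taken. Report each woman's change from that score alongside her raw on-diet scores. Keep taste, emotional eating and social eating as on-diet items only.

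Matching edits:

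- Section 5.2 table: a tick at Start VLCD, marked as these three items only.
- Section 5.2 text: 3-4 occasions in place of 2-3, noting that the first is partial.
- Section 5.1 flow chart: add the three items to the baseline step.
- Section 10.2 form: add a week 0 option.

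The cost is about one minute per woman at a visit that already takes place, with no added procedure or staff. The drawback is that part of a questionnaire described as validated is used at a time point outside its current schedule. The report should say so.

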**5.3 Study Procedure Risks**

Optifast VLCD is accepted as being safe with only minor transient side effects generally insufficient in duration or magnitude to warrant cessation. The main side effects of rapid weight loss and ketosis include cold insensitivity, halitosis, headache, alopecia, irritability, postural hypotension, fatigue, muscle cramps, bowel disturbance (constipation or diarrhoea).

Patients are still eligible for Optifast although extra care should be taken if there is a history of cholelithiasis, pancreatitis or gout as these conditions may flare during rapid weight loss.

Additionally the use of the VLCDs may influence the dosage requirements of some medications, however, patients on sulphonylureas, short and long acting insulins, diuretics for hypertension, medications for hyperlipidaemia, and warfarin are still eligible under medical supervision.

In Australia cancer surgery is normally assigned a clinical urgency Category 1 or 2 which means surgery is performed within 30-90 days of being added to a wait list (AIHW). The 4-6 week time frame will be at the discretion of the Gynaecologic Oncologist.

Venipuncture carries the small risk of swelling, tenderness, or inflammation at the site, vasovagal, infection and thrombosis.

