**The Case for Pre-operative Very Low Calorie Diets (VLCDs) in Obese Endometrial Cancer Patients.**

Version 3

13.08.2017

SYNOPSIS

Protocol title: The Case for Pre-operative Very Low Calorie Diets (VLCDs) in Obese Endometrial Cancer Patients.

Short title: Pre-operative Optifast in Obese Endometrial Cancer Patients.

Protocol version: 3

LIST OF INVESTIGATORS

Principal Investigator: [name]

Organisation: King Edward Memorial Hospital

Address: [name]

[contact]

Email: [contact]

Principal Investigator: [name]

Organisation: St John Of God Subiaco Hospital

Address: [name]

[contact]

Email: [contact]

Associate Investigator: [name] [name]

Organisation: St John Of God Subiaco Hospital

Address: [name]

[contact]

Email: [contact]

Associate Investigator: [name]

Organisation: King Edward Memorial Hospital

Address: [name]

[contact]

Email: [contact]

SUMMARY

Study title: The Case for Pre-operative Very Low Calorie Diets (VLCDs) in Obese Endometrial Cancer Patients.

Short title: Pre-operative Optifast in Obese Endometrial Cancer Patients.

Protocol version: 1

Objectives

Primary objective:

-To evaluate the feasibility of a 4-6 week pre-operative very low calorie diet (VLCD) with Optifast® in severely obese (BMI ≥ 35) low risk endometrial cancer patients (Grade 1 endometrioid adenocarcinoma with no or minimal myometrial invasion) planned to undergo a laparoscopic hysterectomy. Dietary compliance will be assessed by urinary ketone reagent strips.

Secondary objectives:

-To monitor changes over the 4-6 week VLCD period in body weight, BMI, anthropometric measures (hip and waist circumference), clinical variables of blood pressure and biochemical variables (fasting blood sugar and cholesterol).

-To evaluate tolerability of the VLCD using a validated qualitative questionnaire.

-To collect data on surgical outcomes.

Study design: This is a single institution (St John of God Subiaco Hospital) prospective observational study of women in Western Australia diagnosed with low risk endometrial cancer, BMI ≥35, planned to undergo a laparoscopic hysterectomy.

Planned sample size and selection criteria: The study will aim to recruit 20 patients over a 12 month period and will include women recommended to have Optifast as part of their pre-operative preparation for surgery.

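### Gout, gallstone and pancreatitis flares are named as a risk of the diet, but nothing in the protocol systematically records or counts them during the diet period

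*Protocol*

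**What the plan says.** Protocol section 5.3 describes the diet as safe with minor, passing side effects, then singles out three conditions. Women with a history of them stay eligible, but "extra care should be taken if there is a history of cholelithiasis, pancreatitis or gout as these conditions may flare during rapid weight loss".

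What is to be recorded is set out elsewhere:

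- **Primary outcome (2.1).** The number and percentage of women whose urinary ketone tests suggest compliance. Section 3.1 treats a trace or more as adherence.
- **Secondary outcomes (2.2).** Body measurements, "blood pressure and serum biochemistry", a tolerability questionnaire and surgical outcomes.
- **Questionnaire (3.1 and Appendix 10.2).** Six items: taste, hunger, nausea or vomiting, bowel habit, and eating outside the diet for emotional or for social reasons.
- **Complications (3.1).** Listed among the items recorded after the operation, as surgical complications: "urinary tract, vascular or bowel injury; cardiac/pulmonary complications; wound breakdown; infection; estimated blood loss".
- **Visits (5.2).** History is taken at enrolment. Contacts during the diet, and the day of surgery, cover measurements, ketones and the questionnaire.
- **Safety (6.2).** A data monitoring committee meeting after the first six months, and onward communication of issues that patients raise.

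On blood tests, the Summary's secondary objective names "biochemical variables (fasting blood sugar and cholesterol" only. Section 3.1 lists a wider panel that includes "FBC, EUC, LFTs, CMP, uric acid, CA125, iron studies".

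**The concern.** Rapid weight loss is the intended effect of the diet, so section 5.3 describes a harm that the intervention itself may bring about, in women whom the protocol knowingly keeps eligible. The study is meant to document feasibility and tolerability and to supply planning information for a randomised trial. If these events are not asked about, the report has no dependable numerator for them. A reader of the results could not tell whether no woman had an event or no one was asked.

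The primary outcome does not fill the gap. A woman with an attack of gout or biliary pain who keeps to the diet and still passes ketones is a success on that measure, and none of the required fields shows that anything else happened.

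**Working it through.** The protocol gives no flare rate and calls its sample size of 20 pragmatic, so there is no figure to reproduce. The check is of the text, followed by an illustration of scale.

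**Could any planned record capture a flare during the diet?**

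1. Ketone score (2.1, 3.1): no. It measures adherence. A flare that ended the diet might lower the score, but the cause would not be visible.
2. Questionnaire (Appendix 10.2): no item on gout, and none specific to biliary or pancreatic events. Nausea or vomiting is asked but is non-specific.
3. Complication list (3.1): surgical events, recorded post-operatively. The diet period comes before it.
4. History form (Appendix 10.1): completed at the initial visit, with an open past-medical-history heading and no field for any of the three conditions. It comes before the diet and does not reliably identify the women concerned.
5. Blood tests (3.1, 5.2): drawn at baseline and on the day of surgery. Two samples 4-6 weeks apart cannot count clinical events between them.
6. Section 6.2: depends on the patient raising an issue, and nothing requires it to enter the dataset. Section 3.4 plans 24 months of recruitment and data collection, so 24 − 6 = 18 months follow the only scheduled meeting.

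**Biochemistry wording.** The Summary names glucose and cholesterol. Section 2.2 is open-ended, section 3.1 lists the full panel, and section 5.2 describes "additional tests particular to this research (uric acid, iron studies, fasting lipid profile" and others as drawn for this study. Uric acid therefore falls inside section 2.2 and outside the Summary objective. This is a mismatch of wording.

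**Scale (illustration; all rates are assumptions).** With per-woman probability p and m women at risk, the chance of at least one event is 1 − (1 − p)^m.

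| Assumed p | All 20 at risk | Only 3 at risk (assumed number with a history) |
|---|---|---|
| 1% | 1 − 0.99^20 = 18% | 1 − 0.99^3 = 3% |
| 2% | 1 − 0.98^20 = 33% | 1 − 0.98^3 = 6% |
| 5% | 1 − 0.95^20 = 64% | 1 − 0.95^3 = 14% |
| 10% | 1 − 0.90^20 = 88% | 1 − 0.90^3 = 27% |

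**What a count would give.** One event in 20 is 1/20 = 5%. With no events in 20, the exact one-sided 95% upper limit is 1 − 0.05^(1/20) = 13.9%, and the upper end of a two-sided 95% interval is 1 − 0.025^(1/20) = 16.8%. Either limit can be stated only if every woman was asked.

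**The case against.** The strongest reply is that this is an observational study of women receiving the diet as standard care, with fortnightly contact with a dietitian or GP, a committee that discusses safety, and safety concerns listed in section 6.4 as a ground for stopping. A serious flare would probably come to someone's notice, and one that ended the diet might also show in the ketone results. This stands to the extent that a reader should not infer that such an event would necessarily go unreported. It does not supply a count, because the contacts are described as supporting adherence and no event field is attached to them.

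A second reply is that tabulation belongs in the statistical analysis plan. That is right for table layouts, so reference-range shift tables and splits by history are not asked for here. But an analysis plan cannot tabulate data that the protocol does not collect.

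Third, this may be seen as one instance of a wider lack of a structured adverse-event record for the diet period. That is fair, and the fix fits within such a record. The specific case still deserves mention because the protocol names the harm itself.

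Three further stronger readings are tempting and not supported:

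- Women are not admitted because these conditions may flare. Section 5.3 keeps them eligible despite that caution.
- Uric acid and liver function tests are not shut out of the results, since section 2.2 can include them.
- Those tests are not presented as measures of flares. Section 5.2 treats liver function tests as routine care, and the panel names no test for pancreatitis.

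**Conclusion.** The point holds in a limited form. Section 5.3 names a harm of the diet in women kept eligible, and no part of the protocol systematically records or counts it over the 4-6 week diet. The consequence is an incomplete tolerability report. The primary outcome is not biased by this.

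The size cannot be fixed from the document. The range of 18% to 88% for at least one flare assumes rates of 1% to 10% applied to all 20 women. If only three women carried the risk, the same rates give 3% to 27%. The conclusion does not depend on these figures. It rests on the absence of any required field, and on the fact that information not asked for at the time cannot be reliably recovered later.

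The difference in biochemistry wording between the Summary and sections 2.2 and 3.1 is a minor inconsistency to be tidied.

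**What to change.** 1. Record any history of gout, cholelithiasis or pancreatitis explicitly at baseline, as three yes/no fields added to the open past-medical-history heading.
2. Add to the section 5.2 schedule one yes/no line, asking whether a gout, gallstone or pancreatitis event has occurred since the last contact. It belongs at each existing fortnightly contact (it can be asked by telephone) and in the day-of-surgery record.
3. List this event count among the secondary outcomes in section 2.2, and report it out of all enrolled women with an exact binomial interval.
4. Align the biochemistry wording in the Summary with sections 2.2 and 3.1.

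The cost is protocol wording, three baseline fields and one form line at two or three contacts that already take place. No visit or blood sample is added. The tolerability report may look somewhat less favourable, and with 20 women the interval will be wide. Nothing here changes or proposes an eligibility, dose or management rule.
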